## Abstract

**Background:**

Acne vulgaris (AV) is a common chronic dermatologic disease that tends to impair the appearance and quality of life (QoL) of patients. Although several trials have indicated the effectiveness of acupuncture for treatment of patients with AV, the results of these trials have been contested, owing to potential bias in their design. Thus, there is a lack of robust data to evaluate the efficacy of acupuncture in patients with AV. In addition, none of the previous clinical trials of acupuncture therapy for AV used QoL as a primary outcome or employed a sham acupuncture control arm. The aim of the present study is to evaluate the effectiveness of acupuncture in treating the symptoms and QoL of patients with moderate or severe AV.

**Methods/design:**

One hundred eligible participants with AV will be randomly assigned to an acupuncture or a sham acupuncture group (1:1 allocation). All participants will receive 4-week treatment comprising a total of 12 sessions (3 sessions per week). The primary outcome will be change from baseline in the Skindex-16 scale total score at treatment completion. The secondary outcomes will be Skindex-16 subscale score, Dermatology Life Quality Index scale total score, total lesion count and inflammatory lesion count, visual analogue scale scores for assessment of itch and pain, patient expectations of acupuncture, and blinding of the effect of sham acupuncture. Follow-up evaluation will be performed at weeks 16 and 28. All outcome analyses will be performed in the intention-to-treat population.

**Discussion:**

We expect to evaluate the effectiveness of acupuncture in ameliorating the symptoms and improving the QoL of patients with moderate or severe AV compared with sham acupuncture with more robust evidence. The limitations of the trial design are its single-center scope, relatively small sample size, and lack of blinding of the acupuncturists.

**Trial registration:**

Chinese Clinical Trial Registry, ChiCTR-1900023649. Registered on January 2, 2019.

## Background

Acne vulgaris (AV) is a common chronic dermatologic disease involving pilosebaceous units [1, 2]. Skin lesions are the main symptoms of AV; they typically appear over the face, chest, and back [1, 3]. An estimated 79–95% of the adolescent population is affected by AV [4]. The skin lesions include comedones, erythematous papules, pustules, nodules, deep pustules, and scarring. The occurrence of AV lesions on the face may induce anxiety and decrease self-esteem [5, 6], leading to a decline in the quality of life (QoL) [5–8].

The American Society of Dermatology recommends benzoyl peroxide, topical retinoids, or systemic antibiotic therapy as the first-line treatment for mild to severe AV [1–3]. However, these pharmaceutical therapies may cause side effects of drying, peeling, erythema, and skin irritation; in addition, prolonged treatment may result in drug resistance, and the associated recurrence rate is relatively high [9]. Therefore, there is an increasing interest in exploring natural and safe therapies for AV [9, 10]. These natural and safer treatment options include complementary and alternative treatment remedies, such as herbal medicine and acupuncture [9, 10].

Several trials have indicated that acupuncture may alleviate the skin lesions and improve the QoL of patients with AV [11–15]. However, these trials were affected by potential bias due to small sample sizes, nonplacebo/sham/waiting list control, or use of self-defined outcome measures; thus, they did not provide robust evidence of the efficacy of acupuncture in patients with AV. Therefore, we conducted a pilot trial (unpublished) from April 2017 to March 2018 in which 42 patients with moderate or severe AV were randomly allocated to an acupuncture group (*n* = 21) or a sham acupuncture group (*n* = 21). After a 4-week treatment, the number of inflammatory lesions in the acupuncture group (*n* = 21) was 35.62 ± 15.51, with a reduction of 6.62 ± 15.42 from baseline. The number of inflammatory lesions in the sham acupuncture group (*n* = 21) was 30.05 ± 21.16, with a reduction of 15.10 ± 20.13 from the baseline. The difference between the two groups was 8.48 ± 7.74, and there was no significant between-group difference with the *p* = 0.137 due to *p* > 0.05 was considered nonsignificant. These findings contradict the results of previous trials [11–14], and authors of a systematic review of AV also reported that there was no difference between acupuncture and the waiting list for reducing the number of inflammatory lesions [16]. Unlike drugs, which act directly on the pathogen, acupuncture restores normal functions through motivating or inducing the inherent regulatory system [17]. Therefore, acupuncture may relieve other symptoms of AV (itch or pain) [18, 19] and improve the QoL [11]. The Skindex-16 scale is a sensitive and specific tool for assessing the symptoms and QoL of patients with AV, and it includes seven questions related to the symptoms (itch or pain) and characteristics (skin lesions) of AV [20, 21]. Following the 4-week treatment, the total score on the Skindex-16 scale for acupuncture (*n* = 21) was 19.89 ± 15.40, with a reduction of 12.50 ± 19.09 from the baseline. The total score on the Skindex-16 scale for sham acupuncture (*n* = 21) was 30.43 ± 19.39, with a reduction of 0.40 ± 21.12 from the baseline. The difference between the two groups was − 12.9 ± 11, and there was a significant between-group difference in this instance with the *p* = 0.044 due to *p* < 0.05 was considered statistically significant. Therefore, the results of our pilot study indicated that acupuncture may help to relieve total symptoms and improve the QoL of patients with moderate or severe AV. So far, there are two systematic reviews that recommend using the measure of QoL for evaluating the effect of acupuncture on AV [10, 16], but no clinical trials have been conducted that use the measure of QoL to evaluate the effect of acupuncture on the symptoms and the QoL of patients with AV. Therefore, we intend to use the Skindex-16 scale as a primary outcome measure in our planned study to evaluate the effect of acupuncture compared with sham acupuncture on the symptoms and QoL of patients with moderate or severe AV.

## Methods/design

### Study design

The proposed study is a prospective, randomized, sham acupuncture controlled trial with two parallel arms using a 1:1 allocation ratio. The trial will be conducted at the Guang’anmen Hospital, China Academy of Chinese Medical Sciences. The study protocol conforms to the Standard Protocol Items: Recommendations for Interventional Trials (SPIRIT) [22] and the Standards for Reporting Interventions in Clinical Trials of Acupuncture (STRICTA) [23].

### Study recruitment

Participants will be recruited between August 2019 and December 2020 at the Guang’ anmen Hospital via advertisements on posters, the WeChat app, and hospital websites. A dermatologist will be responsible for the screening, which will include diagnosis of the type of acne of patients and a series of physical examinations (discrimination between inflammatory and noninflammatory lesions of AV by the pictures of participants’ faces obtained using a digital camera) according to the diagnostic criteria for AV [2, 24] and the classification of lesions of AV [25], respectively.

All participants will be asked by a research assistant to read the informed consent form that describes the trial, randomization process for treatments, and the potential benefits and risks of the trial. Participants will be informed that both acupuncture and sham acupuncture may be effective for AV, and they will be randomly assigned to the acupuncture group or the sham acupuncture group. Participants will be allowed to withdraw from the trial at any time. Written informed consent will be obtained from all subjects prior to their enrollment.

The demographic and clinical characteristics of the participants at baseline will be recorded by a research assistant: age, sex, race, body mass index (in kg/m^2^), marital status, education level (primary education or below, secondary education, and tertiary education), time of sports activity (0–3 times/month, 1–2 times/week, 3–4 times/week, and ≥ 5 times/week), daily sleep duration (< 7 h, 7–9 h, and > 9 h), smoking history, history of alcohol intake, AV duration in months, and severity of AV as assessed by Global Acne Grading System (GAGS) score (none [0 score], mild [1–18 score], moderate [19–30 score], severe [31–38 score], and markedly severe [> 39 score]) [26].

### Randomization and allocation concealment

The randomization scheme has been prepared by the National Clinical Drug Testing Institute of the Guang’anmen Hospital. Participants will be randomly assigned to receive acupuncture or sham acupuncture treatment in a 1:1 ratio with the fixed block of 4. Sealed opaque envelopes will be used to ensure randomization concealment. The number of the randomization sequence and information on group allocation will be sealed in ordered envelopes. With the inclusion of patients, those envelopes will be opened one by one in sequence. The envelopes will be kept by a research assistant who is not involved in the treatment or assessment. Additionally, assistant researchers will perform a baseline assessment of all participants (− 1 week to 0 week) prior to randomization.

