### Blinding

The participants, outcome assessors, and statisticians will be blinded to the group allocation. However, because of the characteristics of acupuncture, acupuncturists will not be blinded in this trial. To assess the blinding effect of sham acupuncture, participants will be asked to answer the following questions within 5 min after any treatment in week 4: “Do you think you have received traditional acupuncture?” The response options will be “yes,” “no,” or “unclear.” The study protocol is illustrated in Fig. 1.

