### Participants

One hundred eligible participants with AV will be recruited in the trial.

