The sham acupuncture is a crucial tool that can minimize participants’ expectations and the bias of both participants and researchers and assist in the enforcement of blinding [38]. Use of the non-insertion-type needle on nonacupoints was shown to be an optimal method to reduce the possible biological effects [39]. However, the non-insertion-type needle leaves no marks or wounds on the skin. In this condition, the lack of any needle marks may compromise the blinding of participants. Therefore, we will opt for nonacupoints and minimal acupuncture as the sham acupuncture in this trial. Nonacupoints are in proximity to the classical acupoints, which will increase the feasibility of blinding [38]. Meanwhile, using the nonacupoints and minimal acupuncture without any manipulation may minimize actual needle sensation to mitigate the potential physiologic stimulus [38, 40]. The outcome assessors of this study will be blinded to the group allocation, which will also mitigate the lack of acupuncturist blinding.

However, some limitations of our study should be acknowledged. First, the single-center scope of the study and the relatively small sample size may lead to overestimation of the effects of acupuncture. Second, because of the characteristics of acupuncture, the acupuncturist will not be blinded in our trial, which may cause potential bias. Last, it is difficult for the sham acupuncture to be as inert as desired in this trial, owing to a slight stimulus or a stronger stimulus of gentle touch possibly leading to different degrees of neurological responses related to the treatment effect [39, 41]. So, the use of nonacupoints and minimal acupuncture without any manipulation may cause some biological effect leading to false-negative results [36].

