### Trial status

No recruitment currently.

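### A published, fixed block size of 4 at one centre with unblinded acupuncturists leaves concealment open to deduction from past allocations; undisclosed, randomly varying blocks are a cheap improvement

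*Protocol article*

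**What the plan says.** The section Randomization and allocation concealment assigns participants "in a 1:1 ratio with the fixed block of 4". On the safeguard it says: "Sealed opaque envelopes will be used to ensure randomization concealment". The envelopes are numbered, opened in order as patients are included, and held by a research assistant who is kept apart from treatment and assessment. The list has already been prepared by an institute of the same hospital.

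The Study design section describes "two parallel arms using a 1:1 allocation ratio" at one hospital, and the Discussion lists "the single-center scope of the study and the relatively small sample size" among the limitations. No stratification is mentioned.

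On masking, the Blinding section says "The participants, outcome assessors, and statisticians will be blinded to the group allocation", but also that "acupuncturists will not be blinded in this trial". Under Study recruitment, a dermatologist screens and a research assistant handles consent. The Trial status section reads "No recruitment currently".

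**The concern.** Sealed envelopes hide the next card. They do not hide what follows from the cards already opened. With a fixed block of known size, the last assignment of every block is forced by the earlier ones, and the last two are forced whenever the first two match. Here the block size is in print, there seems to be one running sequence, and one group of staff knows the treatments given.

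If knowledge of the next assignment reached the people who decide whether and when a patient enters, enrolment could be timed to the expected arm. Baseline assessment precedes randomization, so severity is known at that moment. Blinding participants and assessors afterwards does not undo selection at entry. The primary outcome is change from baseline in a self-reported quality-of-life score, so a systematic difference between arms in who was enrolled would carry into the main comparison.

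**Working it through.** The article gives no figure for predictability, so there is none to reproduce.

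**Inputs**
- Block size 4, fixed, ratio 1:1 (Randomization and allocation concealment).
- 100 participants (Participants): 100 / 4 = 25 complete blocks.
- One centre (Study design; Discussion).
- Assumption: a single list, since no stratification is stated.
- Assumption about the observer: knows the block size and all earlier allocations in order.

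**Certain allocations, fixed block of 4**

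There are six equally likely blocks. In AABB and BBAA, two positions are forced. In ABAB, ABBA, BAAB and BABA, one is forced.

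- Expected per block: (2 × 2 + 4 × 1) / 6 = 1.333.
- Share: 1.333 / 4 = 33.3%. By position: (0 + 0 + 1/3 + 1) / 4 = 1/3.
- Over 25 blocks: 25 × 1.333 = 33.3 patients.
- Range in a given list: 25 × 1 = 25 to 25 × 2 = 50. Standard deviation: √(25 × 1/3 × 2/3) = 2.4.

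**Best guessing, fixed block of 4**

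The observer always names the arm with more places left in the block. The chances of being right at positions 1 to 4 are 1/2, 2/3, 1/3 × 1 + 2/3 × 1/2 = 2/3, and 1.

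- Sum: 1/2 + 2/3 + 2/3 + 1 = 2.833 per block.
- Rate: 2.833 / 4 = 17/24 = 70.8%, against 50% with no information.

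**Alternatives**

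Fixed blocks of 6 and 8 were enumerated in the same way. Varying blocks were simulated (4,000 lists of 100) for an observer who knows the set of sizes but not their order and updates after each allocation. Run on a fixed block of 4, the simulation returned 33.4% and 70.8%, in agreement with the exact values.

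| Scheme | Certain in advance | Best guess right |
|---|---|---|
| Fixed 4 (plan) | 33.3% | 70.8% |
| Fixed 6 | 25.0% | 68.3% |
| Fixed 8 | 20.0% | 66.6% |
| Random 4/6 | 5.5% | 69.2% |
| Random 4/6/8 | 2.3% | 67.9% |

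Varying the size almost removes certainty. It hardly changes the average guessing rate, because any balanced block still makes the under-represented arm the better bet.

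**Cost in balance**

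If the list is cut inside a block of 8 after four assignments to the same arm, the arms differ by 4. That is the largest final imbalance with sizes 4, 6 and 8.

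**The case against.** The strongest case on the other side is that the one-third figure describes an ideal observer whom the article does not show to exist.

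- **Who knows what.** The Intervention section speaks of acupuncturists in the plural and has participants treated separately. Being unblinded means that each knows the patients they treat. To rebuild the blocks, they would have to pool that knowledge and know the order of randomization. This stands: a reader might infer that acupuncturists see every allocation, and the article does not say so.
- **Separation of roles.** Acupuncturists are given treatment only; screening and consent belong to others. Entry is also limited by a numeric acne-grading range, and baseline is recorded before randomization. This largely stands, with two gaps. An eligible patient's entry can still be brought forward or delayed. The envelope keeper is kept out of treatment and assessment but is not said to be kept out of recruitment, and shares a job title with the person handling consent. A condensed article may leave that detail to the full protocol, so it is a point to settle rather than a fault.
- **Leak to blinded assessors.** A reader might infer that the block size would itself unblind them. It would not: an assessor can deduce a fourth assignment only after learning the first three. A small block can extend a breach but does not start one. Assessor knowledge would also bear more on the photograph-based lesion counts, which are secondary, than on the patient-reported primary outcome.
- **Size of the benefit.** Varying blocks leave the best-guess rate near 68%. This stands, so the case for the change rests on removing certain predictions.

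**Conclusion.** The point holds as a conditional vulnerability with a cheap remedy. Given knowledge of the block size and of all earlier allocations in order, and a single unstratified list, an expected 33 of 100 assignments (25 to 50 in a given list) are certain in advance. The envelopes give no protection against that deduction. The arithmetic is exact; whether anyone at the site would hold this knowledge and act on it cannot be determined from the article.

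A reader might conclude that concealment fails, or that a third of assignments will in practice be foreseen by those who enrol. The article does not support either conclusion: no section gives acupuncturists a part in enrolment, and none describes allocation knowledge reaching screening or consent staff. Equally, none rules it out. The appropriate label is a cheap improvement, not an error in the plan.

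**What to change.** Before recruitment starts:

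1. Have the randomization institute regenerate the 1:1 list with randomly varying block sizes, for example 4, 6 and 8.
2. In Randomization and allocation concealment, replace the fixed block size with: *randomly varying block sizes, not disclosed to staff who recruit, treat or assess until database lock*. Do not print the sizes. The institute belongs to the same hospital, so the restriction should name these roles.
3. State that the envelope keeper takes no part in screening or consent.

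The cost is a new list and a new set of envelopes, plus a possible final difference of up to about 4 patients between arms, which matters little with 100 participants. The article reports no recruitment yet, so the change can be made cleanly. If enrolment has since begun, the unused envelopes can be replaced at the end of a completed block.

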### Blinding

The participants, outcome assessors, and statisticians will be blinded to the group allocation. However, because of the characteristics of acupuncture, acupuncturists will not be blinded in this trial. To assess the blinding effect of sham acupuncture, participants will be asked to answer the following questions within 5 min after any treatment in week 4: “Do you think you have received traditional acupuncture?” The response options will be “yes,” “no,” or “unclear.” The study protocol is illustrated in Fig. 1.

**Fig. 1 Fig1:**
[figure not shown]
Schematic illustration of the study protocol

### Ethical approval

This clinical trial will adhere to the principles of the Declaration of Helsinki and has been approved by the Ethics Committee of the Guang’anmen Hospital (2018-137-KY-01) (see Additional file 1).

### Participants

One hundred eligible participants with AV will be recruited in the trial.

### Inclusion criteria

Individuals aged between 18 and 48 years who qualify for the diagnostic criteria for AV [2, 24]GAGS score between 19 and 38 [26]

### Exclusion criteria

Participants with any of the following conditions will be excluded:
Individuals with polymerization acne, explosive acne, drug acne, premenstrual acne, cosmetic acne, occupational acne, or any other subtypes of acneIndividuals with other severe diseases that may affect acne, such as polycystic ovary syndrome, thyroid disease, or atypical congenital adrenal hyperplasiaIndividuals with other skin diseases that may influence the assessment of AV, such as rosacea, folliculitis, or other skin diseasesIndividuals who have received antibiotics, retinoic acid, steroids, or anti-inflammatory drugs in the preceding 1 monthIndividuals with severe heart, liver, kidney, hematopoietic system or autoimmune disorders, or severe systemic malnutritionPregnant and lactating women or those planning to conceive within 12 monthsIndividuals who have received acupuncture treatment in the past 3 months

### Intervention

All participants will receive treatment for 4 weeks with three sessions per week (ideally every other day), for a total of 12 sessions. Acupuncturists with an undergraduate degree or above and clinical experience of over 1 year at the Guang’anmen Hospital will be responsible for treatment. Participants will be treated separately to avoid communication during the trial period. We will discourage all included participants from receiving any other treatment for AV during the study period. If participants receive any other treatment for AV, they will also be included in this study, and all details of the other treatment for AV will be recorded in the case report form. We will compare the proportion of participants using other treatments between the two groups.

### Acupuncture group

The location of acupoints is described as per the Nomenclature and Location of Acupuncture Points (National Standard of People’s Republic of China, 2006 [GB/T 12346-2006]) [27]. The selection of acupoints will be decided with reference to the Guidelines for AV treatment in China (revised version 2014) [28]. Participants in the acupuncture group will receive stimulation at Dazhui (CV14), bilateral Quchi (LI11), bilateral Hegu (LI4), bilateral Zusanli (ST36), and bilateral Neiting (ST44) with disposable acupuncture needles (0.30 × 40 mm, Huatuo Brand; Suzhou Medical Appliance, Suzhou, Jiangsu, China). After routine disinfection, acupuncture needles will be inserted obliquely into CV14 to a depth of 30–40 mm at an angle of 15–30 degrees; acupuncture needles will be vertically inserted into bilateral LI11, bilateral LI4, bilateral ST36, and bilateral ST44 to a depth of 25–30 mm three times (once every 10 min) with slight lifting, thrusting, and twisting manipulations to produce a sensation of de-qi. Each session of acupuncture will last 30 min.

### Sham acupuncture group

Participants in sham acupuncture group will receive sham acupuncture at sham CV14 (10 mm to CV14), LI11 (10 mm to LI11), LI4 (10 mm to LI4), ST36 (25 mm to ST36), and ST44 (10 mm to ST44) with disposable acupuncture needles (0.30 × 25 mm, Huatuo Brand). Sham CV14, LI11, LI4, ST36, and ST44 will be vertically inserted to a depth of 1–2 mm without any manipulation and de-qi. The treatment sessions will last 30 min.

Participants will not be allowed use of other treatments for AV throughout the trial. Detailed information pertaining to use of other treatments will be recorded in the case report form.

